## Abstract

**Background:**

We aimed to evaluate the acceptability and efficacy of two brief, Internet-delivered cognitive behavioural therapy interventions—*MUMentum Pregnancy* (study 1) and *MUMentum Postnatal* (study 2)—in reducing maternal symptoms of anxiety, depression and overall psychological distress compared to usual care in the perinatal period.

**Methods/Design:**

Women who are pregnant (study 1) or < 12 months postpartum (study 2) with current clinically elevated symptoms of anxiety and/or depression according to validated self-report measures, will be recruited via the research arm of a not-for-profit clinical and research unit in Australia and randomised to the intervention group or treatment as usual control group. The minimum sample size for each study (alpha 0.05; power 0.80 for a *g* of 0.80) was identified as 50 with at least 10% more to be recruited to account for expected attrition. The co-primary outcome measures are the Patient Health Questionnaire 9-item scale and Generalised Anxiety Disorder 7-item scale to measure depression and anxiety symptom severity, respectively, and will be administered at the following primary time-points: baseline; post treatment; and at one-month follow-up. Psychological distress will be measured according to the Kessler-10 psychological distress scale at each primary time-point and will also be completed before each lesson for those in the intervention group. The total trial period nine weeks for study 1 and 11 weeks for study 2. Program efficacy will be determined using intent-to-treat mixed models. Maintenance of gains will be assessed at one-month follow-up.

**Discussion:**

The current randomised controlled trial seeks to extend the literature by evaluating the efficacy of a self-help intervention for women in the perinatal period. If efficacious, the *MUMentum* programs have the potential to be easily disseminated via https://thiswayup.org.au/ to large numbers of women across Australia as an intervention for women screening positive for anxiety, depressive or distress symptoms during pregnancy or postpartum.

**Trial registration:**

Australian New Zealand Clinical Trials Registry, ACTRN12616000560493; ACTRN12616000559415. Registered on 2nd May 2016.

**Electronic supplementary material:**

The online version of this article 10.1186/s13063-017-2422-5) contains supplementary material, which is available to authorized users.

## Background

Maternal anxiety and depression is common during the perinatal period (i.e. pregnancy through to 12 months postpartum) [1, 2]. Prevalence rates estimate up to 20% of women will experience clinically significant symptoms of anxiety or depression during this time, with symptoms often co-occurring [3, 4]. Yet fewer than half of these women will seek help or receive evidence-based treatment [1, 5, 6]. Women face many structural and attitudinal barriers to accessing and engaging with treatment including lack of time, cost, geographical distance to services, transport issues, and practical difficulties with childcare [5, 7–9]. Women are also often unwilling to disclose problems associated with motherhood to partners, family and health professionals due to perceived social stigma (e.g. pressure to minimise emotional difficulties as a mother) [1, 7].

In the absence of routine screening in community-based and hospital-based settings, clinically significant symptoms of perinatal anxiety and depression remain under-detected and undertreated [2, 10]. This is a significant problem given anxiety and depression are associated with short-term and long-term adverse outcomes for the mother and infant (e.g. increased risk of obstetrical complications, poor birth outcomes and child developmental problems; detrimental to the mother–infant relationship) [11–14]. If left untreated, perinatal anxiety and depression can also lead to a chronic or recurring course of symptoms throughout the mother’s life [6]. Developing evidence-based treatments that are acceptable and easily accessible for perinatal women (e.g. no referral required; minimal logistical issues) is an important area of focus that warrants attention.

One approach to help increase access to treatment is through the use of Internet-delivered psychological interventions, particularly cognitive behavioural therapy (CBT). In comparison to face-to face treatment, Internet-delivered CBT (iCBT) is scalable (e.g. does not rely on clinician time and resources in order to be disseminated at a population level), available at a reduced cost, more accessible especially for rural and remote patients, and can be completed at home offering increased convenience to the patient [15, 16].

Preliminary research suggests that iCBT is efficacious for women with depression in the perinatal period. One randomised controlled trial (RCT) [17] evaluated a therapist-assisted six-session iCBT intervention, *MumMoodBooster*, for women with a clinical diagnosis of postpartum depression. This multimedia intervention included weekly therapist coaching via telephone. Post treatment, depression symptom severity scores were significantly lower for the intervention group compared to the treatment as usual (TAU) control condition (Cohen’s *d* = 0.83), with 79% of women in the intervention group no longer meeting diagnostic criteria for depression at 12 weeks, compared to 18% in the TAU control condition. Adherence and patient satisfaction with the program was also high. Pugh et al. [18] conducted an RCT to evaluate a seven-session iCBT intervention, *Maternal Depression Online*, for women with symptoms of subthreshold and clinical postpartum depression. This multimedia intervention included weekly therapist support and encouragement via email. For those in the iCBT group, symptoms of postpartum depression were significantly reduced from pre to post treatment and maintained at four-week follow-up compared to those participants in the waitlist control condition. Acceptability of the program and therapeutic alliance was reported as high.

Only one RCT [19] has evaluated an antenatal iCBT intervention for women with a clinical diagnosis of depression during pregnancy. The ten-week guided intervention, delivered as an adjunct intervention in addition to usual antenatal care, was supported by a CBT-trained therapist who provided regular feedback and encouragement. Compared to the TAU control group, depression scores significantly reduced from pre to post treatment for the iCBT group, with a large between-groups effect (Hedge’s *g* = 1.21). Treatment credibility and satisfaction with the intervention was high.

As this area of research is still in its early stages, there are significant gaps in the literature that need to be addressed. Although perinatal anxiety is reported to have similar prevalence rates to perinatal depression [3], and the two disorders are often highly co-morbid [20], no Internet-delivered interventions have targeted the reduction of maternal anxiety symptoms alone or anxiety symptoms co-morbid with depression. Given that anxiety and depression are thought to share similar aetiological and maintenance processes [21–23], transdiagnostic iCBT, which targets these shared factors, is a promising avenue for the treatment of anxiety or depression in perinatal women. Transdiagnostic iCBT interventions have the potential to teach treatment principles that can be generalised across anxiety and depressive diagnoses [24], as well as educate women about symptoms of both anxiety and depression regardless of whether they meet clinical levels. It has also demonstrated efficacy in treating primary and co-morbid anxiety and depression in the general adult population [25, 26].

ICBT for women in the antenatal period has also received limited attention, with only one study having evaluated an iCBT intervention for antenatal depression [19]. This is surprising given that antenatal anxiety and depression are two of the strongest predictors of postpartum depression [27, 28]. In addition, research to date has focused only on the evaluation of six- to seven-session ‘guided’ interventions for perinatal depression which are supported by trained therapists. No studies have evaluated brief (i.e. < 6 sessions) or ‘unguided’ (i.e. no therapist assistance) interventions for anxiety and/or depression in either the antenatal or postpartum period.

## Objectives

The primary aim of the proposed studies is to test the acceptability and the efficacy of the iCBT *MUMentum* programs—*MUMentum Pregnancy* (study 1) and *MUMentum Postnatal* (study 2)—in reducing symptoms of anxiety, depression and overall psychological distress compared to usual care in the perinatal period. We hypothesise that the two iCBT interventions will significantly reduce symptoms of distress, anxiety and depression and will be significantly more effective than usual care. The secondary aim is to explore the effects of the iCBT programs on mother–infant bonding, parenting confidence and maternal quality of life. We hypothesise that the iCBT programs will lead to significant improvements in these three factors compared with usual care.

## Methods

### Design

Both studies are parallel group, CONSORT-revised 2010 compliant [29] superiority RCTs of iCBT program vs TAU control. Study 1 is a nine-week trial, including baseline data collection, four-week intervention period, one-week post-treatment evaluation and one-month follow-up. Study 2 is an 11-week trial, including baseline data collection, six-week intervention period, one-week post-treatment evaluation and one-month follow-up. The current trial protocol has been approved by the Human Research Ethics Committee of St. Vincent’s Hospital, Sydney (HREC/16/SVH/63). Both studies are registered with the Australian New Zealand Clinical Trials Registry (study 1: ACTRN12616000560493; study 2: ACTRN12616000559415).

### Study setting

The Clinical Research Unit for Anxiety and Depression (CRUfAD) is a non-profit joint initiative of St. Vincent’s Hospital, Sydney and the University of New South Wales (UNSW), School of Psychiatry, Sydney, Australia. CRUfAD specialises in the development, evaluation and dissemination of evidence-base CBT programs via https://thiswayup.org.au/. These RCTs will be conducted within CRUfAD’s clinical research arm, the Virtual Clinic (https://virtualclinic.org.au/). The mode of Internet recruitment and delivery enables potential participants from all Australian states to apply for enrolment in the current trials, with no face-to-face contact required.

### Participants and recruitment

Participants will be recruited through flyers (located in public maternity hospitals in Sydney and GP clinics Australia-wide), paid Internet advertising (e.g. Facebook via THIS WAY UP Clinic) and word of mouth (e.g. midwives, general practitioners [GPs], obstetricians; conference presentations).

#### Inclusion criteria

Both studies will recruit adult women aged > 18 years, who are 13–30 weeks pregnant (study 1) or within 12 months postpartum (study 2). Applicants will meet clinical cut-off scores (>9) for anxiety and/or depressive symptoms as measured on the Generalised Anxiety Disorder 7-item version (GAD-7) [30] and Patient Health Questionnaire 9-item version (PHQ-9) [31]. Additional inclusion criteria are as follows: computer and Internet access; Australian resident; fluent in written and spoken English; willing to provide name, phone number and address, and to provide the name and address of their GP.

#### Exclusion criteria

Both studies will exclude applicants who report current substance abuse or dependence; a diagnosis of schizophrenia or bipolar disorder; current use of benzodiazepines or who have recently started psychological therapy for depression/anxiety (<4 weeks) or medication for depression/anxiety (<8 weeks). Applicants reporting current suicidality (indicated by a score of 3 to item 9 of the PHQ-9; and/or a score of 2 or 3 to item 9 of the Beck Depression Inventory, version 2 (BDI-II) [32]; and/or severe depression (indicated by score ≥ 23 on PHQ-9) [31] will also be excluded. Applicants that self-report occasional thoughts of suicidality (indicated by a score of 1 or 2 to item 9 of the PHQ-9; and/or score of 1 to item 9 of the BDI-II) will be contacted by the study clinician for a risk assessment telephone interview and if not suitable (i.e. endorse current suicidality) will be excluded.

### Procedures

#### Online application and psychological assessment

The enrolment and study procedure are outlined in Fig. 1. All women apply online through the Virtual Clinic website (https://virtualclinic.org.au/) and are required to provide electronic informed consent, personal contact details and GP contact details. Applicants will then complete online screening questionnaires to determine suitability. There are three outcomes for all online applications: (1) applicants that do not meet inclusion criteria will be notified on-screen and via email that they are not suitable; (2) applicants who meet inclusion criteria yet indicate possible risk of suicidality, will be ‘pending’ until a telephone risk interview (by the supervising clinician) can be conducted to determine suitability for inclusion into the study; and (3) applicants that meet all inclusion criteria and indicate no risk of suicidality will proceed to randomisation.

**Fig. 1 Fig1:**
[figure not shown]
*Flowchart* illustrating enrolment and study procedure

All applicants that do not meet inclusion criteria will receive information on alternative services and encouraged to discuss their symptoms with their GP. All GPs of applicants that are excluded on severe depression and/or current suicidality criteria will be notified via letter that their patient applied for this study and was excluded on this basis.

#### Randomisation and allocation procedures

Online applications meeting the study’s inclusion criteria will be randomised to either iCBT or a TAU control group according to a 1:1 ratio within blocks of 20. Because the two trials were conducted using different software, the randomisation procedure differs slightly between the studies.

For study 1, the allocation sequence will be generated by an independent person not involved in the study, using a random number generator (https://www.random.org/). The numbers corresponding to the treatment group (1 = iCBT) or the control group (2 = TAU) will be placed in sequentially numbered, sealed opaque envelopes. The randomisation envelopes will then be assigned manually (by the study coordinator) to the successful online application in order of application date. Once matched, the group allocation will be revealed and participants will be notified of their group allocation by e-mail.

For study 2, which will be conducted in an updated Virtual Clinic web system,^1^ the randomisation sequence will be electronically uploaded to the server by an independent person not involved in the study. Successful applicants will be notified via e-mail of their acceptance into the study and automatically randomised to treatment group (1 = CBT) or control group (2 = TAU).

Once randomised, participants and research personnel will not be blinded to group condition. Participants in the intervention group and control group will login to https://virtualclinic.org.au/ and complete baseline (pre-treatment) questionnaires. The three primary data collection points for study participants in iCBT group and TAU group are as follows: baseline (pre-treatment), post treatment, and at one-month follow-up (see Fig. 2). Participants will receive notifications and reminders to complete questionnaires via computer-generated emails, SMS and follow-up phone calls from the research team. We will track reasons for non-adherence (e.g. lost to follow-up). As this is an unguided program, participant enquiries (e.g. technical issues) will be responded to by research technicians; no coaching or support with program content will be provided.

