**Fig. 2 Fig2:**
[figure not shown]
Schedule of enrolment, interventions and assessments

Participants allocated to the iCBT group will receive access to the *MUMentum* program via their Virtual Clinic account. All three lessons are required to be completed within the active treatment period, with one lesson released every seven days. The treatment period for study 1 is four weeks, which allows participants up to one week to complete each lesson and an additional week for revision. For study 2, the treatment period is six weeks, to allow participants up to two weeks to complete each lesson (without a revision week). Time to complete lessons was increased for study 2 as it was predicted this would be more suitable for postnatal women who are time-poor and adjusting to and caring for a newborn. There will be a five-day lockout period between lessons to ensure participants spend time revising and implementing the lesson material before moving onto the next lesson. At the beginning of each lesson, participants will complete the Kessler-10 psychological distress scale (K10) [33] as a brief measure of psychological distress, as well as two brief questions relating to time spent completing the previous lesson and homework activities. Participants will be notified of new lessons and reminded to stay on schedule via email and SMS reminders. One week after the active treatment period ends, participants will receive post-treatment questionnaires, with follow-up questionnaires completed four weeks later.

Participants allocated to the TAU group will receive access to questionnaires at each primary data collection point (i.e. baseline, post treatment, follow-up) via their Virtual Clinic account. The total trial period is nine weeks for study 1 and 11 weeks for study 2. As this is a ‘treatment as usual’ controlled study, all participants in the control group will have access to their usual care (i.e. continuation of their current maternity care). Information will be collected from participants regarding usual care. For ethical reasons, participants in the TAU group will be offered access to both the *MUMentum Pregnancy* and *MUMentum Postnatal* iCBT programs at conclusion of the study period.

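### The PHQ-9 and GAD-7 scores called baseline are self-reports taken after unblinded randomisation, although both scales are already measured before randomisation at screening

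*Protocol article*

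**What the plan says.** Under Inclusion criteria, eligibility rests on the two co-primary scales: "Applicants will meet clinical cut-off scores (>9) for anxiety and/or depressive symptoms as measured on the Generalised Anxiety Disorder 7-item version (GAD-7") and the PHQ-9. Under Online application and psychological assessment, these come first: "Applicants will then complete online screening questionnaires to determine suitability". The next step for a suitable applicant is allocation: "applicants that meet all inclusion criteria and indicate no risk of suicidality will proceed to randomisation". No baseline step is described between the two.

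Under Randomisation and allocation procedures, study 1 tells women their group: "Once matched, the group allocation will be revealed and participants will be notified of their group allocation by e-mail". For study 2 the wording is "Successful applicants will be notified via e-mail of their acceptance into the study and automatically randomised to treatment group", without saying when the group itself becomes known. For both studies: "Once randomised, participants and research personnel will not be blinded to group condition". The sentence that follows is "Participants in the intervention group and control group will login to https://virtualclinic.org.au/ and complete baseline (pre-treatment) questionnaires". The text below Fig. 2 agrees with that order for the control arm: "Participants allocated to the TAU group will receive access to questionnaires at each primary data collection point (i.e. baseline, post treatment, follow-up").

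Statistical Methods plans intent-to-treat REML mixed models. If effects are significant, the arms are then contrasted on mean post-treatment and follow-up scores. The section also plans between-group Hedges' g, within-group Cohen's d, significance tests of arm differences on pre-treatment measures, and a missing-at-random check that compares women with and without missing data on baseline measures. It does not say which score is the analysis baseline or how that score enters the model.

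**The concern.** Randomisation guarantees comparability only for what is measured before the allocation is known. Here the pre-treatment reference is a self-report given once a woman can know whether she receives the programme now or only when the study ends. Relief, disappointment or expectancy could change her answers, and could do so differently by arm. The protocol itself treats expectancy as worth measuring.

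Several planned analyses lean on this score: the omnibus test that triggers the pairwise contrasts (if it is a group-by-time test), the within-group d, and the arm comparison at baseline, where a difference could reflect knowledge of allocation rather than chance. The dropout analysis is also affected. A woman who leaves between allocation and this questionnaire has no score at the baseline time-point, so a check built on that time-point cannot cover her, and such loss may differ by arm. The attrition allowance is at least 10% of 25, or about three women per arm.

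**Working it through.** **1. The plan's own figure.** Inputs from Statistical Methods: g = 0.80, alpha 0.05, power 0.80, 25 per group. By the normal approximation, n = 2(1.960 + 0.842)² / 0.80² = 24.5, so 25 per group. The exact t-test gives 25.5, so 26, with power 0.791 at 25. One-sided alpha would give 20, so the figure is two-sided. The stated size reproduces, and nothing below changes it.

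**2. Order of steps.** Screening with PHQ-9 and GAD-7; randomisation; group disclosed (stated for study 1, inferred for study 2); login and baseline questionnaires. The reference score is therefore a post-randomisation measurement, and a pre-randomisation score on each of the same scales exists.

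**3. Effect of a shift.** Suppose knowledge of allocation moves one arm's reported baseline by δ SD, uniformly, and leaves later scores alone. Let ρ be the baseline-outcome correlation.

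- Group-by-time or change-based contrast: bias = δ in size.
- Baseline-adjusted contrast: bias ≈ ρδ.
- Between-group contrast of post-treatment means, with each arm's mean free at each time: bias = 0, because the shift is absorbed by that arm's own baseline mean.
- Any of these with the screening score as baseline: bias from this source = 0.

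**4. Numbers.** Neither δ nor ρ is in the documents. Assume δ = 0.1, 0.2, 0.3 and ρ = 0.3 to 0.7, with 25 per arm and no true effect. The standard errors in SD units are √(2(1−ρ))·√(2/25) for change and √(1−ρ²)·√(2/25) for the adjusted contrast. Two-sided type I error is 1 − Φ(1.96 − bias/SE) + Φ(−1.96 − bias/SE).

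Example: for δ = 0.2 and ρ = 0.5, √(2/25) = 0.283. Change: SE = 0.283, bias/SE = 0.707, type I error = 0.109. Adjusted: bias = 0.10, SE = 0.866 × 0.283 = 0.245, bias/SE = 0.408, type I error = 0.069.

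| δ (assumed) | Change: bias | Change: type I error | Adjusted: bias | Adjusted: type I error |
|---|---|---|---|---|
| 0.1 | 0.10 | 0.060–0.074 | 0.03–0.07 | 0.051–0.064 |
| 0.2 | 0.20 | 0.092–0.150 | 0.06–0.14 | 0.056–0.107 |
| 0.3 | 0.30 | 0.146–0.278 | 0.09–0.21 | 0.063–0.180 |

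Relative to the planned 0.80, the change-based bias is 0.1/0.8 = 12.5% to 0.3/0.8 = 37.5%.

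**The case against.** The strongest reply is that the only between-group comparison the plan spells out is of mean post-treatment and follow-up scores. With free arm-by-time means, a uniform baseline shift does not bias it. That stands. A reader might infer that every treatment estimate in the trial is contaminated; the text does not support this. What remains exposed is the omnibus test if it is a group-by-time test (the section does not name it), any baseline-adjusted estimate, the within-group d and the baseline comparisons.

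Other stronger readings also go too far:

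- **That women without a baseline are excluded after randomisation.** Nothing makes a completed baseline a condition of entering the intent-to-treat analysis. A woman who skips it can still contribute later scores, and she has screening scores.
- **That study 2 women are shown to know their group.** Their e-mail announces acceptance. Prior knowledge of the group follows only from the no-blinding sentence and the order of the text.
- **That the plan rejects the screening scores as baseline.** It does not say which score enters the model. Figs. 1 and 2 and any SAP are not at hand. The text does describe a separate login after allocation.
- **That control women are refused the programme.** Their access is deferred to the end of the study.

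The mechanism may also be weak: both scales ask about the past two weeks, which may largely precede allocation. That limits the plausible δ but does not make it zero.

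**Conclusion.** The point holds as a weakness in sequencing. The score labelled pre-treatment is collected after unblinded randomisation, explicitly in study 1 and by inference in study 2. Under the assumed δ of 0.1 to 0.3 SD, the possible bias is 0.1 to 0.3 SD in a change-based test and about 0.03 to 0.21 SD in a baseline-adjusted one. It is zero, for a uniform shift, in a post-treatment contrast with free arm-by-time means. This is a risk of unknown size and direction, not a demonstrated difference, and no figure in the protocol is wrong because of it. It merits correction because an unaffected measurement of each co-primary scale already exists.

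**What to change.** Pre-specify the pre-randomisation screening PHQ-9 and GAD-7 as the baseline covariate in the primary mixed model for the corresponding scale, with post-treatment and follow-up scores as outcomes and all randomised women in the intent-to-treat set. Use the same screening scores in the dropout analysis, so that women who leave straight after allocation are covered. Label the later questionnaire as post-randomisation, and keep within-group effect sizes descriptive. If the screening scores are already meant to be the baseline, it is enough to say so.

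The cost is a change of wording in the analysis plan; the sample size stays at 25 per group. The screening score is somewhat older and partly range-restricted (above 9 on at least one of the two scales, PHQ-9 below 23), so it will explain slightly less variance. The restriction applies equally to both arms, so regression to the mean does not bias the comparison between them.

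Releasing the questionnaires before allocation for the remaining recruits is optional. Trial status reports 98 women randomised across the two studies, against a minimum of 2 × (50 + 5) = 110. The change would reach few women if recruitment stops near that minimum, and would mix pre- and post-allocation baselines within a trial.
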